**11.1.4. Unexpected Serious Adverse Reaction or Suspected Unexpected Serious Adverse Reaction (SUSAR)**

Any adverse reaction, the nature, frequency, outcome or severity of which is not consistent with the applicable Reference Safety Information (RSI): Summary of the Product Characteristics (SmPC) of Daclatasvir, and Sofosbuvir.

**11.1.5. Adverse event of special interest (AESI)**

AESI will be considered as SAEs and therefore declared as such to the promoter.

For this research, AESI include:

- Any grade 4 biological or clinical event;
- Any event leading to permanent or temporary discontinuation of the investigational medicinal product;
- Any hepatitis B virus (HBV) reactivation
- Cardiac arrhythmias

**11.1.6. New fact**

A new fact is defined as any safety data that could modify significantly the evaluation of the benefit/risk ratio of the investigational medicinal product or the clinical trial, likely to affect the safety of participants or that could modify the investigational medicinal product administration,

the trial documentation or the conduct of the trial, or to suspend or interrupt or modify the protocol or similar trials.

Examples: a serious adverse event which could be associated with the trial procedures and which could modify the conduct of the trial, recommendations of the DSMB, if any, where relevant for the safety of subjects.

## 11.2. Responsibilities of the investigator

The investigator should:

- Report any non-serious AEs in the proper CRF AE form.
- Report any SAEs and AESI as a detailed, written report, using "SAE initial notification form" (in CRF SAE section), and notified to the sponsor, immediately and no later than 24h after being made aware of it.
- Ensures that all relevant information is forwarded to the sponsor within 7 days after the initial notification.
- Send to the sponsor all relevant documentation related to reported SAE (e.g. hospitalization report, laboratories results...), without omitting to make it anonymous and note the identification number of the participant in the trial.
- Follow any SAE until participant's clinical recovery is complete and laboratory results have returned to normal or baseline, or until the event has stabilized (even if the participant left the trial, when the SAE is possibly related to the study drug).
- Report all new relevant information on SAE or AESI using "SAE complementary notification form" (in CRF SAE section) and notified to the sponsor.
- Report any pregnancy and its outcome, concerning the enrolled woman, as a detailed, written report, using the "Initial pregnancy notification form" and notified to the sponsor, immediately and no later than 48 hours after being made aware of it.
- Follow the subject until the end of the pregnancy or its interruption and to notify the outcome to the sponsor using the "Final pregnancy notification form" (CRF).

### **Warning:**

If the pregnancy outcome fulfilled a seriousness criteria (eg: **anomaly or birth defect, fetal death, voluntary or therapeutic interruption of pregnancy, miscarriage needed a hospitalization**), the investigator has to notify it to the sponsor as an SAE.

Any AE must be reported, if it occurs for a participant, throughout the duration of the research, therefore from the moment the subject signed the informed consent and until the end of the follow-up of the participant.

SAE occurring to a subject after the treatment of that subject has ended should be reported to the sponsor if the investigator becomes aware of them, specially if related to the study drug. The investigator does not need to actively monitor subjects for adverse events once the trial has ended, unless provided otherwise in the protocol.

**Notification:**

The investigator sends the SAEs, pregnancies recorded in corresponding form of the CRF, dated and signed, with all relevant anonymized documentation related to the SAE (e.g. hospitalization report, laboratories results...), to the Clinical Project Manager of the CTU, by email: [[contact]](mailto:[contact])

Then the CTU will send, immediately the eCRF SAE notification form and all documentation related to the SAE, to the Inserm-ANRS Pharmacovigilance unit, by [contact] or by email: [[contact]](mailto:[contact])

**11.2.1. AE evaluation****The adverse event**

The investigator should assess, if possible, the diagnosis of all adverse events. Diagnosis, or if not available, syndrome should be reported whenever possible.

Date of “event onset” on an adverse event should be earlier (or the same day) than date of seriousness.

When medical or surgical procedures (e.g.: surgery, endoscopy, tooth extraction, transfusion) occurred; the condition that leads to the procedure should be notified.

**The severity**

The severity (i.e. intensity) of all AE should be graded using the appropriate table below and reported by the investigator in the corresponding form of the CRF.

**“ ANRS scale to grade the severity of AE in adults” (see appendix)****The seriousness**

For any AE, the investigator must determine whether the event meets one or more of the severity criteria previously described.

Deaths must be reported for subjects as the outcome of an adverse event and not as an adverse event itself if the cause is known. If the cause is unknown, the death should be reported as “unknown cause of death”.

## The causality

The investigator must assess the causality of all AE in relation to the study drug, concomitant medication and the research, using the definitions below.

- Reasonably possible related: there are facts (evidence) or arguments to suggest a possible or potentially possible causal related.
- Not reasonably possible related: the event seems to be more related to other causes than to the study drug, such as the patient's clinical condition (underlying pathology, medical history, etc.) or a concomitant drug (without pharmacological interaction with the drug tested).

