#### **Patients with HBV co-infection**

All patients with HCV active infection will be tested for HBsAg at inclusion. If HBsAg is positive, a treatment by tenofovir will be initiated from inclusion until 12 weeks after discontinuation of HCV treatment.

In case of sudden rising of ALT level during follow-up of HCV treatment, HBV DNA will be performed to eliminate reactivation of occult HBV infection and a treatment by tenofovir could be initiated in case of positive result.

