#### **Risk related to HVC treatment and stopping rules**

For risk management of suspected adverse event, please refer to each Interventional Medicinal Product SmPC.

For combination daclatasvir/sofosbuvir:

- Patient treated with combination daclatasvir based regimen should be under close surveillance by their investigators for signs and symptoms of hypersensitivity. Hypersensitivity reactions are mostly characterized by rash, constitutional findings, and sometimes, organ dysfunction, including hepatic failure, pulmonary and renal dysfunctions. Patient should contact his/her investigator promptly if he/she develops a rash. The investigator will determine if the symptoms should be considered as potential hypersensitivity. In case of rash grade 2 or 3, dual daclatasvir based regimen could be temporally or definitely discontinued by the investigator. Discontinue daclatasvir based regimen and other suspect agents immediately if signs or symptoms of severe skin reactions or hypersensitivity reactions develop (including, but not limited to, severe rash

or rash accompanied by fever, general malaise, fatigue, muscle or joint aches, blisters, oral lesions, conjunctivitis, facial oedema, hepatitis, eosinophilia, angioedema).

- Clinical status including liver aminotransferases should be monitored. In case of elevated aminotransferase, the investigator should report to the Decision Support Committee which will provide recommendations about further investigations and potential treatment discontinuation. The decision to discontinue temporally study drugs should be documented in the CRF. All definitive study drugs discontinuation will be declared to the clinical study manager of the CTU. After study drugs been discontinued, the patient will remain in the protocol and will be followed according the calendar scheduled by the protocol if he accepts.
- Concomitant use of certain molecules with sofosbuvir and daclatasvir may require patient close monitoring (clinical or biological) when initiating or during the treatment. This is notably the case of amiodarone, beta-blockers, diabetic medication and antagonist vitamin K. Refer to the respective SmPC of sofosbuvir and daclatasvir.

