### **11.3. Responsibilities of the sponsor**

#### **11.3.1. Recording and assessment of SAE**

The sponsor

- Keep detailed records of all SAE which are reported to him by investigators.
- Assesses the causality of the SAE in relation to the study drug, concomitant medication (in case of drug-drug interaction) and the research.

In the absence of information on causality from the reporting investigator, the sponsor should consult the reporting investigator and encourage him to express an opinion on this aspect.

The causality assessment given by the investigator should not be downgraded by the sponsor. If the sponsor disagrees with the investigator's causality assessment, the opinion of both the investigator and the sponsor should be provided in the report to the National Competent Authority.

All SAE for which the investigator or the sponsor considers that a causal relationship is a reasonable possibility are considered as suspected SAR.

- Assesses if the SAE is expected or not using the applicable Reference Safety Information.

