## **Role**

The DSMB is a consultative board for the scientific committee and to the sponsor. Its members will provide general advice on the progress of the trial, including the rate of inclusions, the quality of follow-up, the overall rate of drug-related adverse events, changes in biological markers, the overall incidence of primary outcomes, and the number of subjects needed.

They will help to make difficult decisions that require an independent assessment while the trial is underway. Advice may be needed regarding:

- Premature discontinuation of the trial (because the rate of adverse events is high, the trial is no longer feasible, or the available data are sufficient);
- Substantial changes to the protocol that becomes necessary during the inclusion or follow-up phases, or to account for new scientific information.

The DSMB will conduct and interpret intermediate analyses, if any.

At the end of each meeting, a written report containing the DSMB's opinion will be sent to the sponsor and the members of the scientific committee.

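### The two causality categories for adverse events overlap and leave a gap, so the drug-related rate may be low or inconsistent, chiefly for non-serious events

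*Protocol*

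**What the plan says.** Section 11.2.1 of the Protocol, under The causality, sets the task: "The investigator must assess the causality of all AE in relation to the study drug, concomitant medication and the research, using the definitions below". Two definitions follow.

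- Related: "Reasonably possible related: there are facts (evidence) or arguments to suggest a possible or potentially possible causal related".
- Not related: "Not reasonably possible related: the event seems to be more related to other causes than to the study drug". The examples given are the patient's own condition and a concomitant drug that does not interact with the study drug.

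For serious events, section 11.3.1 adds a second assessor. The sponsor makes its own causality assessment and may not downgrade the investigator's. It then applies this rule: "All SAE for which the investigator or the sponsor considers that a causal relationship is a reasonable possibility are considered as suspected SAR".

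The label is put to use in section 12.2 (Role), where the DSMB's advice covers "the overall rate of drug-related adverse events". Safety of the 12-week regimen is a secondary objective (section 4). Section 7 measures the treatment-phase endpoints in the total population without comparing arms, and section 3 (Study main hypothesis) says that the treatment strategy is not compared.

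**The concern.** A two-label rule should place every event under exactly one label. This one uses two different kinds of threshold. The first asks whether anything points to the drug. The second asks whether something else points more strongly elsewhere, and it does not require that evidence for the drug be absent. Two careful investigators can therefore label the same event differently, and both will have followed the protocol.

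The comparative test also departs from the standard used in the next step. Section 11.3.1 asks only whether a causal relationship is a reasonable possibility. A relationship can be a reasonable possibility even when another cause is more likely, yet the investigator's definition allows such an event to be filed as not related.

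At stake is the drug-related rate the DSMB is asked to consider. With no untreated or differently treated group, no comparison of overall event rates is available to correct a poor split between related and unrelated events.

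**Working it through.** No arithmetic applies. The protocol gives no drug-related event rate, and the point rests on no sample size or power figure. The check is logical: take the two features that the definitions use and see which label each combination receives.

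Feature E: there are facts or arguments for a possible link to the drug. Feature A: another cause seems likelier than the drug.

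| Case | E | A | Meets related? | Meets not related? | Result |
|---|---|---|---|---|---|
| a | yes | no | yes | no | related |
| b | yes | yes | yes | yes | both, no tie-break |
| c | no | yes | no | yes | not related |
| d | no | no | no | no | neither |

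Case b shows that the labels are not mutually exclusive. Case d shows that they are not exhaustive.

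Next, follow a case b event that the investigator files as not related.

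1. **Non-serious, not of special interest.** Section 11.2 sends it to the adverse event form of the CRF. Section 11.3.1 gives the sponsor a causality assessment for serious events only. No second assessment is described, so the event leaves the drug-related count.
2. **Serious, or of special interest.** Section 11.1.5 treats events of special interest as serious. These are grade 4 events, events leading to temporary or permanent discontinuation, hepatitis B reactivation and cardiac arrhythmias. Section 11.2 sends them all to the sponsor with no causality filter. Under section 11.3.1 the event is a suspected serious adverse reaction if either assessor sees a reasonable possibility. It is missed only if the sponsor also rejects the link. The protocol does not say whether the sponsor uses the section 11.2.1 definitions, so a smaller risk remains.
3. **Total counts.** Section 8 (Treatment follow-up) has all adverse events documented whatever their possible causality. The totals do not change; only the split into related and unrelated does.

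Last, test the proposed redefinition, under which an event is not related only if E is absent. Cases a and b become related, and cases c and d become not related. Every event then has one label, and the investigator's test no longer depends on ranking causes.

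**The case against.** The strongest reply is that the first definition is very broad. An investigator who reads it first would label a case b event related, so the text shows ambiguity and not a fixed bias. That stands. Under-counting is the likely direction only where the comparative test is applied. Case d may also be uncommon, since onset during treatment may itself be taken as an argument for the drug.

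It can also be said that relatedness is not the only safety information. Aminotransferases and creatinine are measured at weeks 4, 8 and 12, the DSMB also looks at biological markers, and raised aminotransferases go to the Decision Support Committee. This is correct, and it limits the harm. But that committee advises on investigation and management, and no role in the causality label is given to it.

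A reader might infer more than the protocol supports in four ways.

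- *That SUSARs are under-counted.* This does not follow. Every serious event reaches the sponsor, who assesses it, may not downgrade it, and can make it a suspected reaction alone.
- *That liver and kidney events are bound to be lost to the underlying disease.* Section 11.2.2 does mention "organ dysfunction, including hepatic failure, pulmonary and renal dysfunctions", but as an occasional feature of hypersensitivity reactions that mostly show as rash. It does not list them as stand-alone drug reactions.
- *That tenofovir reactions are wrongly excluded.* For HBsAg-positive patients section 8 says "a treatment by tenofovir will be initiated from inclusion". An event due to tenofovir alone is nevertheless correctly unrelated to the study drug, and the definition sets aside concomitant drugs only where there is no interaction.
- *That a percentage can be put on the loss.* Any such figure would need an assumed number of events and an assumed share relabelled, neither of which the protocol gives.

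**Conclusion.** The defect is real but narrow. The two labels in section 11.2.1 are neither exclusive nor exhaustive, they have no tie-break, and the comparative one conflicts with the standard in section 11.3.1. This is a rule stated wrongly, not detail left for a later document.

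The consequence is a risk, not a certainty: drug-related events may be too few or inconsistently labelled in the rate that goes to the DSMB. It falls chiefly on non-serious events that are not of special interest. Serious events and events of special interest are partly protected by the sponsor's assessment; how far depends on which definition the sponsor applies, and the protocol is silent on that. The size cannot be computed from the documents.

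The primary endpoint, testing uptake, is untouched. No endpoint in section 7 uses drug-relatedness: treatment failure refers to discontinuation for adverse events or death without asking for a causal link. The conclusion assumes that some events will show both evidence for the drug and a likelier other cause, and that at least some investigators will apply the second definition to them.

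**What to change.** In section 11.2.1, make three changes.

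1. Define the not-related label as the absence of any fact or argument for a possible causal relation.
2. State that an event meeting the first definition is related even when another cause seems likelier.
3. State, with a matching line in section 11.3.1, that the sponsor applies the same definition to serious events and events of special interest.

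The cost is a few sentences in the protocol and a short note to those who complete the forms. Somewhat more events will be labelled related, so the reported drug-related rate may look slightly less favourable. No treatment rule or endpoint changes.

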### **11.2.2. Potential risks of the research and management guidelines in case of adverse event or pregnancy occurrence**

#### **Risk related to capillary and blood sample**

Capillary sampling from a finger, is a medical procedure, which may be performed on patients of any age, for specific tests that require small quantities of blood, and for patient's diagnosis, management and treatment.

Main risk for blood sample with is :

- Infection (abscess)
- Pain
- Hematoma on site injection

However the tests are carried out by professionals and precautions are used to prevent these risks.

#### **Risk related to HVC treatment and stopping rules**

For risk management of suspected adverse event, please refer to each Interventional Medicinal Product SmPC.

For combination daclatasvir/sofosbuvir:

- Patient treated with combination daclatasvir based regimen should be under close surveillance by their investigators for signs and symptoms of hypersensitivity. Hypersensitivity reactions are mostly characterized by rash, constitutional findings, and sometimes, organ dysfunction, including hepatic failure, pulmonary and renal dysfunctions. Patient should contact his/her investigator promptly if he/she develops a rash. The investigator will determine if the symptoms should be considered as potential hypersensitivity. In case of rash grade 2 or 3, dual daclatasvir based regimen could be temporally or definitely discontinued by the investigator. Discontinue daclatasvir based regimen and other suspect agents immediately if signs or symptoms of severe skin reactions or hypersensitivity reactions develop (including, but not limited to, severe rash

or rash accompanied by fever, general malaise, fatigue, muscle or joint aches, blisters, oral lesions, conjunctivitis, facial oedema, hepatitis, eosinophilia, angioedema).

- Clinical status including liver aminotransferases should be monitored. In case of elevated aminotransferase, the investigator should report to the Decision Support Committee which will provide recommendations about further investigations and potential treatment discontinuation. The decision to discontinue temporally study drugs should be documented in the CRF. All definitive study drugs discontinuation will be declared to the clinical study manager of the CTU. After study drugs been discontinued, the patient will remain in the protocol and will be followed according the calendar scheduled by the protocol if he accepts.
- Concomitant use of certain molecules with sofosbuvir and daclatasvir may require patient close monitoring (clinical or biological) when initiating or during the treatment. This is notably the case of amiodarone, beta-blockers, diabetic medication and antagonist vitamin K. Refer to the respective SmPC of sofosbuvir and daclatasvir.

### **11.3. Responsibilities of the sponsor**

#### **11.3.1. Recording and assessment of SAE**

The sponsor

- Keep detailed records of all SAE which are reported to him by investigators.
- Assesses the causality of the SAE in relation to the study drug, concomitant medication (in case of drug-drug interaction) and the research.

In the absence of information on causality from the reporting investigator, the sponsor should consult the reporting investigator and encourage him to express an opinion on this aspect.

The causality assessment given by the investigator should not be downgraded by the sponsor. If the sponsor disagrees with the investigator's causality assessment, the opinion of both the investigator and the sponsor should be provided in the report to the National Competent Authority.

All SAE for which the investigator or the sponsor considers that a causal relationship is a reasonable possibility are considered as suspected SAR.

- Assesses if the SAE is expected or not using the applicable Reference Safety Information.

### **11.3.2. Reporting of safety data to the National Competent Authority and the Ethics Committee**

#### **11.3.2.1. SUSAR reporting (Suspected Unexpected Serious Adverse Reaction)**

All Suspected Unexpected Adverse Reactions (SUSAR) have to be reported, within the legal timeframe, by the sponsor to Ethic Committee and DSMB.

The timelines for expedited initial reporting (day 0) starts as soon as the information containing the minimum reporting criteria has been received by the sponsor.

For fatal and life-threatening SUSAR, the sponsor should report within 7 calendar days.

SUSAR which are not fatal and not life-threatening are to be reported within 15 calendar days.

If significant new information on an already reported case is received by the sponsor, this information should be reported as a follow-up report within 8 days after being made aware of the relevant complementary information.

